#### Syndemic outcomes

The syndemic outcomes are premature mortality and all-cause hospitalisation. Mortality data are obtained from the death register based on death certificates held within the NHS Digital (England and Wales) and the NHS Central Register (Scotland) between 01/01/2011 and 30/09/2021. All-cause hospitalisation data are obtained from the Hospital Episode Statistics data - Admitted Patient Care (England), Scottish Morbidity Records – General / Acute Inpatient and Day Case Admissions (Scotland), and Patient Episode Database (Wales) between 01/01/2011 and 28/02/2018.

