### NHANES methods

#### Design and study population

The NHANES program is conducted in 2-year cycles by the Centers for Disease Control and Prevention. Data are obtained from self-reported questionnaires, clinical examinations and lab tests. Each cycle includes nearly 10,000 participants and is representative of the United States population across all age groups. In this project, NHANES cycles between 2009 and 2014 will be used due to required data availability and consistency. Attempts to harmonise variables’ selection across NHANES and UK BioBank databases are made.

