#### Syndemic outcomes

The syndemic outcomes are premature mortality and all-cause hospitalisation. Mortality data are obtained from the National Death Index (available up to 31 December 2015). All-cause hospitalisation data are based on being hospitalised in the year preceding the survey.

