#### Syndemic constructs

Syndemic constructs include social adversity (socioeconomic adversity) and mental, physical and oral multimorbidity. No data is available in NHANES on traumatic events.

Socioeconomic adversity will be measured by SEP indicators at individual and household levels: education, employment, occupation, income and health insurance. Education is measured at an individual level and will be categorised into high (college or above) and low (high school diploma or below). Employment status is measured at an individual level and will be grouped into: employed (working at a job or business or with a job or business but not at work) and unemployed (looking for work or not working at a job or business). Occupation is measured using socioeconomic index, which is based on the employees’ earnings, education level and prestige. It will be categorised based on the median into upper and lower level and unemployment. The lower level will include retirees and students. Income is measured by family income ratio to the federal poverty line (<100%, 100%-199%, 200%-399%, >400%). Health insurance will be categorised into private health insurance (including any private health insurance, Medi-Gap or single-service plan), public health insurance only (including Medicare, Medicaid, State Children’s Healthcare Plan, military healthcare, Indian Health Service, State Sponsored Health Plan or other government programme) and no health insurance. No data is available in NHANES on area deprivation.

Mental multimorbidity will include depression (“moderately-severe” or “severe” depressive symptoms versus “moderate”, “mild” or “no” depressive symptoms; as measured by the PHQ-9) and severe mental illness (as measured by medicines prescribed in the past month for severe mental illness).

Physical multimorbidity will be measured using Ronaldson et al. approach (**Supplementary Table 1**) (28). However, not all the 36 long term physical health conditions are reported in NHANES (such as bronchiectasis, psoriasis and polycystic ovarian syndrome). Only those that are available in NHANES will be used to indicate the physical multimorbidity construct.

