Oral multimorbidity will include the presence of moderate and severe periodontal disease, tooth loss (as a continuous and categorical variable: being edentate versus dentate), number of decayed teeth (as a continuous and categorical variable: having no decayed teeth versus having one or more decayed teeth), self-reported oral pain in the past year (“very often”, “fairly often” or “occasionally” versus “hardly ever” or “never”) and self-report global oral health (“excellent”, “very good” or “good” versus “fair” or “poor”). Periodontal disease (moderate and severe versus mild or no periodontal disease) will be measured by the clinical attachment loss (CAL) and periodontal probing depth (PPD). Severe periodontitis is defined as having 2 or more interproximal sites with CAL 6 mm or greater (not on the same tooth) and 1 or more interproximal sites with PPD 5 mm or greater. Moderate periodontitis is defined as 2 or more interproximal sites with CAL 4 mm or greater (not on the same tooth) or 2 or more interproximal sites with PPD 5 mm or greater (also not on the same tooth). Mild periodontitis is defined as 2 or more interproximal sites with CAL 3 mm or greater and 2 or more interproximal sites with PPD 4 mm or greater (not on the same tooth) or 1 or more sites with 5 mm or more.

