#### Statistical analysis

Descriptive statistics will be used to summarise participants characteristics. For NHANES and RELACHS data, survey analysis procedures will be used to account for the sample weights, stratification and clustering of the complex sampling design to ensure representative estimates.

To answer the research questions on the presence of syndemic relationships, a structural equation modelling (SEM) technique will be utilised to conceptualise syndemic constructs and model complex relationships between directly observed and indirectly observed (latent) variables. The SEM technique has gained increasing popularity in syndemic research (30, 31). To use this technique, the following steps will be undertaken:

In step one, exploratory and confirmatory factor analyses will be used to identify the clustering nature and reduce the number of indicators (observed variables) under each theoretical construct. In step two, a SEM to predict premature mortality and all-cause hospitalisation, controlling for age, sex and ethnicity, will be run. Analysis will include identifying whether the indicators chosen to measure the latent constructs are acceptable. confirmatory factor analysis will be used to provide information on how indicator items measure underlying (latent) constructs. In step three of the analysis, SEM will be used to examine the direct and indirect relationships between the constructs. The goodness of fit (GoF) of the SEM model to the data will be assessed considering the indices of Comparative Fit Index (CFI) and Tucker-Lewis Index (TLI; where values >.90 indicate a good fit), root mean square error of approximation (RMSEA), and Standardised Root Mean Square Residual (SRMR; where value <.05 indicate a good fit). In step four, the synergistic (multiplicative) interactions between different latent constructs and measured variables will be tested using two-step estimation procedures (32).

To answer the question on whether syndemic relationships vary by age, sex and ethnicity, stratified analyses by age, sex and ethnicity will be performed.

Full Information Maximum Likelihood technique will be used as a pragmatic approach for data missing estimation for SEMs. This approach produces unbiased parameter estimates and standards errors (33). For UK BioBank and RELACHS datasets, stability of exposure data over time will be checked by calculating the intraclass correlation coefficients between baseline and follow up data.

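### NHANES hospitalisation is counted in the year before the survey that measures the time-varying constructs and mediators, yet it is modelled as a predicted outcome with indirect paths

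*Protocol article*

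**What the plan says.** The NHANES outcomes are premature mortality and all-cause hospitalisation. On the second, the protocol article (NHANES methods, Syndemic outcomes) says: "All-cause hospitalisation data are based on being hospitalised in the year preceding the survey". Exposures and mediators come from the survey itself: "Data are obtained from self-reported questionnaires, clinical examinations and lab tests" (Design and study population). The severe mental illness indicator is defined "as measured by medicines prescribed in the past month for severe mental illness", and one oral indicator is "self-reported oral pain in the past year" (Syndemic constructs). Mediators are health behaviours and CRP.

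The Statistical analysis section, written once for all datasets, says in step two that "a SEM to predict premature mortality and all-cause hospitalisation, controlling for age, sex and ethnicity, will be run". Step three examines direct and indirect relationships between the constructs, and step four tests synergistic interactions. The NHANES research question is worded identically to the UK Biobank one and asks about syndemic relationships impacting mortality burden and all-cause hospitalisation.

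In UK Biobank, participants were recruited from 2006 to 2010 and admissions are counted "between 01/01/2011 and 28/02/2018".

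**The concern.** A predictive or mediating path needs the predictor, and then the mediator, to come before the outcome. In NHANES the admission is already over when most changeable inputs are recorded. An admission can lead to a new prescription, a new diagnosis, low mood, lost work or income, changed behaviour or raised CRP, and each of these is an input to the model. A coefficient from such a variable to hospitalisation mixes any forward effect with the effect of the admission on the variable.

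At stake is the interpretation of the NHANES hospitalisation results in steps two to four and in the analyses stratified by age, sex and ethnicity. They would be reported as predictive and mediating effects whose direction the data cannot support.

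**Working it through.** No sample size, power or event figure bears on this point, and the plan gives no figure to reproduce. The check sets the stated time windows side by side, with the NHANES survey at month 0.

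- **Outcome, hospitalisation:** months −12 to 0. No admission after the survey is counted.
- **CRP, body mass index, oral examination, and employment and insurance status:** recorded at month 0, after every counted admission.
- **Depression score, income and current behaviours:** collected at the survey. The article gives no reference period for most of them.
- **Medicines for severe mental illness:** months −1 to 0, the last month of the outcome window.
- **Oral pain:** months −12 to 0. This coincides with the outcome window, so the order is undetermined.
- **Education, edentulism, attachment loss, established long-term conditions, lifetime smoking, ever addicted:** recorded at month 0 but probably begun earlier. The article does not date onset.

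**Indirect paths.** The indirect effect is a × b, where a is the path from construct to mediator and b the path from mediator to outcome. With CRP at month 0 and the admission somewhere in months −12 to 0, b asks a later blood value to transmit an effect to an earlier event. It could be read forwards only if CRP at month 0 stood in for CRP before the admission. The plan does not state that assumption. Its check of exposure stability over time, by intraclass correlation between baseline and follow-up, is planned for UK Biobank and RELACHS only.

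**What the rest of the analysis can do.** Adjustment for age, sex and ethnicity does not restore the order. Nor do the fit indices (CFI, TLI, RMSEA, SRMR), since a model with an arrow reversed can fit equally well.

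**Contrast within the plan.** UK Biobank recruitment ends in 2010 and admissions count from 01/01/2011, so the order is right for variables measured at recruitment. RELACHS takes constructs from phase 1 and the outcome from phase 3, and notes that oral data exist only in phase 3. For NHANES the article discloses the lack of data on traumatic events and area deprivation, but not the reversed outcome window. No lag, restriction or cross-sectional label appears.

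**Mortality as the alternative outcome.** The death index runs to 31 December 2015 and the cycles cover 2009 to 2014. If surveys ran from the start of 2009 to the end of 2014 (an assumption), maximum follow-up is 2015 − 2008 = 7 years for the earliest participants and 2015 − 2014 = 1 year for the latest.

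**The case against.** **Recording is not onset.** A periodontal measurement at month 0 does not mean the disease arose after an admission in the previous year, and a past-month prescription may mark a long-standing illness. This stands. It limits the point to variables that can change within a year, and to the mediators.

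**A tempting magnitude.** A reader might note that 11 of the 12 outcome months precede the medicine window, and that all 12 precede the examination and blood sample, and take those shares as the size of the problem. They describe when things were recorded and say nothing about the amount of bias.

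**Reverse causation as the whole explanation.** A reader might also infer that the NHANES hospitalisation results could be due to reverse causation alone. The documents do not support that. It is plausible for mood, CRP, employment, income and recent prescriptions, and implausible for education or edentulism.

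**Replication.** The article never says that NHANES will replicate UK Biobank. It mentions only attempts to harmonise variable selection, and plans no pooling or formal comparison. This also stands. What remains is that the same question is put to both datasets, so a reader needs to be told that the two hospitalisation results differ in kind.

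**Wording.** *Predict* is ordinary regression language in a section shared by all datasets, and the look-back year is openly stated. That is fair as to the one word. It does not answer the indirect paths or the NHANES question's own use of *impacting*.

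**Conclusion.** The point holds for NHANES all-cause hospitalisation and the time-varying constructs and mediators. Direction cannot be established for them, and indirect paths through CRP or current behaviours run against time. Long-standing indicators are less affected. This is a conflict between an outcome window and a directed analysis that the article itself fixes, so it is not a detail left to a fuller document.

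The reach is one of two NHANES outcomes in one of three datasets. NHANES mortality is untouched, as is UK Biobank hospitalisation for variables measured at recruitment; the article does not date every UK Biobank variable. The amount of bias cannot be computed from the document. The conclusion assumes that survey measures reflect status at or near the survey unless a longer window is stated, and that the long-standing indicators mostly predate the admission year.

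**What to change.** 1. Analyse NHANES prior-year hospitalisation as a labelled cross-sectional association, with no mediators and no indirect effects. Describe any interaction term for it as association only.
2. Remove *predict* and *impacting* for this outcome, and amend the NHANES research question to match.
3. Rest directed NHANES inference on mortality.
4. State that the NHANES hospitalisation result is not comparable with UK Biobank hospitalisation, which is counted after recruitment.

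The cost is wording and one fewer directed model; no new data are needed. The downside is real: NHANES loses any predictive claim about hospitalisation, and its directed SEM then depends on mortality with follow-up ending on 31 December 2015, about a year at most for the latest participants. That limit should be stated beside the mortality results.

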#### Syndemic constructs

Syndemic constructs include social adversity (socioeconomic adversity) and mental, physical and oral multimorbidity. No data is available in NHANES on traumatic events.

Socioeconomic adversity will be measured by SEP indicators at individual and household levels: education, employment, occupation, income and health insurance. Education is measured at an individual level and will be categorised into high (college or above) and low (high school diploma or below). Employment status is measured at an individual level and will be grouped into: employed (working at a job or business or with a job or business but not at work) and unemployed (looking for work or not working at a job or business). Occupation is measured using socioeconomic index, which is based on the employees’ earnings, education level and prestige. It will be categorised based on the median into upper and lower level and unemployment. The lower level will include retirees and students. Income is measured by family income ratio to the federal poverty line (<100%, 100%-199%, 200%-399%, >400%). Health insurance will be categorised into private health insurance (including any private health insurance, Medi-Gap or single-service plan), public health insurance only (including Medicare, Medicaid, State Children’s Healthcare Plan, military healthcare, Indian Health Service, State Sponsored Health Plan or other government programme) and no health insurance. No data is available in NHANES on area deprivation.

Mental multimorbidity will include depression (“moderately-severe” or “severe” depressive symptoms versus “moderate”, “mild” or “no” depressive symptoms; as measured by the PHQ-9) and severe mental illness (as measured by medicines prescribed in the past month for severe mental illness).

Physical multimorbidity will be measured using Ronaldson et al. approach (**Supplementary Table 1**) (28). However, not all the 36 long term physical health conditions are reported in NHANES (such as bronchiectasis, psoriasis and polycystic ovarian syndrome). Only those that are available in NHANES will be used to indicate the physical multimorbidity construct.

Oral multimorbidity will include the presence of moderate and severe periodontal disease, tooth loss (as a continuous and categorical variable: being edentate versus dentate), number of decayed teeth (as a continuous and categorical variable: having no decayed teeth versus having one or more decayed teeth), self-reported oral pain in the past year (“very often”, “fairly often” or “occasionally” versus “hardly ever” or “never”) and self-report global oral health (“excellent”, “very good” or “good” versus “fair” or “poor”). Periodontal disease (moderate and severe versus mild or no periodontal disease) will be measured by the clinical attachment loss (CAL) and periodontal probing depth (PPD). Severe periodontitis is defined as having 2 or more interproximal sites with CAL 6 mm or greater (not on the same tooth) and 1 or more interproximal sites with PPD 5 mm or greater. Moderate periodontitis is defined as 2 or more interproximal sites with CAL 4 mm or greater (not on the same tooth) or 2 or more interproximal sites with PPD 5 mm or greater (also not on the same tooth). Mild periodontitis is defined as 2 or more interproximal sites with CAL 3 mm or greater and 2 or more interproximal sites with PPD 4 mm or greater (not on the same tooth) or 1 or more sites with 5 mm or more.

#### Mediators

Mediators are health behaviours and lifestyle, and C reactive protein.

Health behaviours and lifestyle variables will include obesity (BMI>=30), alcohol intake (healthy versus unhealthy level; the former is defined as daily consumption of one drink or fewer for women and two drinks or fewer for men, according to the dietary guidelines in the US - one drink contains 14g of ethanol in the US), smoking (healthy versus unhealthy levels; the former is defined as never smoked or smoking fewer than 100 cigarettes in life), physical activity (healthy versus unhealthy; the former is defined as 150 minutes of moderate-intensity physical activity weekly or 75 minutes of high-intensity physical activity weekly), poor appetite or overeating (Yes versus No), diet quality (healthy versus unhealthy; the former is defined as the health eating index in the top two fifths of distribution), trouble falling/staying asleep or sleeping too much (Yes versus No), ever addicted to any substance or behaviour (Yes versus No), number of sexual partners in the past year, inconsistent condom use (“never” versus “occasionally” or “always”), toothbrushing (twice daily versus less than twice daily), dental flossing (once daily versus less than once daily) and dentist visiting (once every two years or more versus less than once every two years).

The level of CRP is used as a marker of bodily inflammation and presented in mg/L.

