#### Mediators

Mediators are health behaviours and lifestyle, and C reactive protein (as an indicator of systemic inflammation).

Health behaviours and lifestyle variables will include obesity (BMI>=30), alcohol intake (healthy versus unhealthy level; the former is defined as daily consumption of two drinks or fewer for men and women, according to the dietary guidelines in the UK - one drink contains 8g in the UK), smoking (healthy versus unhealthy levels; the former is defined as never smoked or smoking fewer than 100 cigarettes in life), physical activity (healthy versus unhealthy; the former is defined as 150 minutes of moderate-intensity physical activity weekly or 75 minutes of high-intensity physical activity weekly), poor appetite or overeating (Yes versus No), diet quality (healthy versus unhealthy level; the former is defined as meeting at least five out of the following ten dietary recommendations: 3 servings/day of fruit, 3 servings/day of vegetables, 3 servings/day of whole grains, ≥2 servings/week of (shell)fish, 2 servings/day of dairy, 2 servings/day of vegetable oils, ≤2 servings/day of refined grains, ≤1 serving/week of processed meats, ≤2 servings/week of unprocessed meats, and no sugar-sweetened beverages) (26, 27), trouble falling/staying asleep or sleeping too much (Yes versus No), ever addicted to any substance or behaviour (Yes versus No), and lifetime number of sexual partners.

The level of C-reactive protein (CRP) is used as a marker of bodily (systemic) inflammation and presented in mg/L.

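### Diet is reduced to yes/no, and BMI to obese or not, before mediation is estimated; if these enter as observed binary mediators, part of their indirect effect is counted as direct

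*Protocol article*

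**What the plan says.** Two Mediators sections of the protocol article fix the coding.

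- **NHANES, diet quality.** It is healthy or unhealthy, where "the former is defined as the health eating index in the top two fifths of distribution". The cut is relative to the sample and puts 40% above it.
- **UK BioBank, diet quality.** It is also healthy or unhealthy, with healthy meaning "meeting at least five out of the following ten dietary recommendations". The article does not give the share who meet this.
- **Both databases, BMI.** It is used only as obesity, at 30 or above. The share is again not given.

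Not every mediator is cut. CRP is kept as a level ("The level of CRP is used as a marker of bodily inflammation and presented in mg/L"), and the number of sexual partners has no cut-point. In the NHANES oral multimorbidity construct, tooth loss and decayed teeth are each carried in both continuous and categorical form. No such provision is made for diet or BMI.

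Under Statistical analysis, step three states that "SEM will be used to examine the direct and indirect relationships between the constructs". The section allows both observed and latent variables. It does not say whether the lifestyle variables enter singly or as one latent construct, or how binary variables are linked.

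**The concern.** A mediator analysis credits the indirect path with whatever the recorded mediator explains. The healthy eating index and the ten-item count are graded. Two people in the unhealthy group can differ widely in diet, and if adversity is one reason for that, the difference still reaches the outcome. A yes/no mediator cannot see it, so a linear model with the binary variable as an observed mediator adds it to the direct effect of adversity.

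This is bias and not loss of precision, so the size of UK BioBank or NHANES does not remove it. What is at stake is the statement of how much of the relation between adversity and mortality or hospitalisation runs through diet and body weight: the behavioural route would look weaker, and the direct route stronger, than they are.

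The point does not depend on detail that may stand in a fuller analysis plan. The article itself fixes the binary coding and names no continuous version.

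**Working it through.** The article gives no mediation or power figure to reproduce. The check asks how much of an indirect effect survives the cut.

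**Inputs**

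- From the article: share above the NHANES diet cut, p = 0.40.
- Assumed: one mediator M with a standard normal score; standardised exposure-to-mediator path a from 0 to 0.5; linear effect b of M on the outcome; the binary D (1 if M is above the cut) entered as an observed variable.

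**Formulas**

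1. Squared correlation of the score with its cut version: λ = φ(z)² / [p(1 − p)], where φ is the normal density at the cut.
2. The slope of D on the exposure is aφ. The coefficient of D on the outcome, given the exposure, is bφ(1 − a²) / {p(1 − p)(1 − a²λ)}. Their product is the estimated indirect effect: ab × λ(1 − a²) / (1 − a²λ).
3. Share moved to the direct path: 1 − λ(1 − a²) / (1 − a²λ).

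**NHANES diet cut**

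λ = 0.3863² / (0.40 × 0.60) = 0.622.

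- a = 0: 1 − 0.622 = 38% moved.
- a = 0.1: 1 − 0.622 × 0.99 / (1 − 0.01 × 0.622) = 38%.
- a = 0.3: 1 − 0.622 × 0.91 / (1 − 0.09 × 0.622) = 40%.
- a = 0.5: 1 − 0.622 × 0.75 / (1 − 0.25 × 0.622) = 45%.

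A simulation of 2,000,000 records gave 39%, 40% and 45% at a = 0.1, 0.3 and 0.5. As an example, take a = 0.3, b = 0.3 and a direct effect of 0.200. The true indirect effect is 0.3 × 0.3 = 0.090. The cut model reports 0.054, and the missing 0.036 raises the direct effect to 0.236.

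**BMI cut (share assumed, since the article gives none)**

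| Assumed share above cut | λ | Moved, a = 0 to 0.5 |
|---|---|---|
| 0.35 | 0.603 | 40-47% |
| 0.25 | 0.539 | 46-53% |
| 0.20 | 0.490 | 51-58% |

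No figure is put on the UK BioBank diet count. Its share above the cut is unknown, and a 0-10 count is not normal.

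**Other specifications that the article leaves open**

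- Binary variable modelled as a threshold on a latent normal response: at a = 0.3 the estimate is 0.090 against a true 0.090, so about 0% is moved.
- One latent lifestyle factor with eight binary indicators: 0.0854 against 0.090, so about 5%.
- True effect acting only at the cut: the binary mediator loses about 0% (−0.3% to 0.4% in simulation at the 40% cut).

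**What the continuous score costs in the case least favourable to it**

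Suppose the effect acts only at the cut, with size 0.6. The covariance of D with M, after the exposure is removed, is φ(1 − a²), and the residual variance of M is 1 − a². The coefficient of M is therefore 0.6φ and the indirect effect is 0.6aφ, which is the whole of it. Under joint normality, the continuous score keeps the direct/indirect split even when the cut is the truth.

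**The case against.** The strongest reply is that the shift assumes a model that the article does not commit to. Step one reduces indicators under each construct by factor analysis, step three speaks of relations between constructs, and health behaviours are listed as one group. A latent lifestyle factor is a natural reading, and the shift is then small. This stands, and it makes the size conditional. It does not remove the point. Mediators are listed apart from the syndemic constructs, so single observed entry is equally natural. The 5% figure also assumes that the behaviours act only through their common factor.

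Other replies:

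- **Obesity is a named condition.** This stands. BMI at 30 or above is not an arbitrary split, so BMI is the weakest of the three cases and calls only for a sensitivity analysis.
- **The UK BioBank diet rule is referenced, and the two databases are meant to be harmonised.** A reference may support the rule as a description of diet; it does not make the effect on the outcome a step at five. Harmonisation is a fair aim, but a sample-relative cut in one database and an absolute count in the other do not give a common scale.
- **Alcohol and activity are cut as well.** True, and the same mechanism could apply. The point is limited to the two diet scores and BMI, which must exist as graded values before they are cut.
- **Several correlated mediators may absorb part of the residual.** Possible. The calculation has a single mediator and does not cover this.

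**Conclusion.** The point holds in conditional form and is worth acting on. If diet and BMI enter step three as observed binary mediators of graded effects, part of their indirect effect is reported as direct. For the NHANES diet cut this is about 38-45% of that one pathway, given an approximately normal score, linear effects and an exposure path of up to 0.5. Mortality and hospitalisation are not linear outcomes, so the figure is a guide to size. Under the latent treatments above, or with an effect only at the cut, it is about 0-5%.

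A reader might infer three stronger things that the document does not support.

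- That 40% or more of every indirect effect is lost. CRP and number of sexual partners are not cut, and the article fixes a share above the cut only for NHANES diet.
- That the evidence for a syndemic is inflated. The Introduction defines a syndemic by synergistic interaction, which step four tests. A shift between direct and indirect paths is not a shift in that test. Nor was any overstatement of the multimorbidity paths computed.
- That power is materially reduced. The article states no power target, and the databases hold 502,412 participants (UK BioBank) and nearly 10,000 per cycle (NHANES).

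**What to change.** In the two Mediators sections, state that step three uses the healthy eating index as a continuous score (NHANES) and the diet score as the 0-10 count (UK BioBank). Keep the healthy/unhealthy versions for description and for one sensitivity analysis. Keep obesity as defined, and add a sensitivity analysis with BMI continuous or in ordered bands.

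The cost is a few sentences and no new data, since each score has to be computed before it can be cut. Two small downsides follow: diet effects are expressed per unit or per standard deviation instead of healthy versus unhealthy, and the linearity of the diet and BMI relations with the outcome must be checked.
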